#### Feasibility outcome measures

Proportion of approached patients who consent to participation.Proportion of participants who receive the allocated intervention.Proportion of participants who complete both CPETs.Proportion of participants who did not withdraw.Proportion of participants who received the allocated intervention and completed both CPETs without withdrawing.Proportion of participants who were compliant with wearing wrist accelerometers.Rate of patient recruitment at each trial centre.Time (days) from providing consent to first CPET and from CPET to fistula disconnection.Patient and healthcare professional perceived acceptability of trial design and processes (qualitative assessment carried out by interviews).

#### Clinical outcome measures

Peak VO_2_ as measured during incremental CPET on a cycle ergometer.Physical functioning domain score of Short Form-36 Quality of Life questionnaire.^38^Activity levels (mean daily Euclidean norm minus one) as calculated from accelerometry data collected from provided wrist-worn accelerometer device over 7-day period at baseline and following 6-month assessment.Serum N-terminal pro B-type natriuretic peptide value.Office blood pressure.Additional CPET indices: ventilatory anaerobic threshold, endurance time, peak workload, O_2_ pulse, VO_2_/work rate slope (VO_2_/WR), minute ventilation/CO_2_ output slope (VE/VCO_2_), heart rate/VO_2_ slope (HR/VO_2_), perceived exertion rating (Borg scale).Additional domain scores of the Short Form-36 QoL questionnaire^38^: physical role limitation, emotional role limitation, energy/ fatigue, emotional well-being, social functioning, pain, general health, perceived health change.Kidney transplant function (eGFR by CKD-EPI estimation^37^).Fistula-related symptoms reported in modified Vascular Access Specific QoL questionnaire^39^ (for all participants at enrolment, and at 6 months for cohort randomised to standard care).Proportion of participants with at least one major adverse cardiovascular event (MACE)^40^: cardiovascular death; ischaemic cardiovascular event (myocardial infarction, percutaneous coronary intervention, coronary artery bypass graft); hospitalisation for heart failure at any time during the 6-month study period.

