### Outcomes

For this feasibility study, the primary outcome measure will be the proportion of approached patients who complete the study, defined as the proportion of eligible approached patients that consent, receive the allocated intervention, and complete both CPET tests without withdrawing.

Secondary outcomes are subdivided into: those related to the feasibility of the study; clinical measures that will be measured at baseline and 6 months following intervention, and the differences in these values; and safety outcome measures occurring between study consent and the 6-month assessment visit.

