### Sample size

As this is a feasibility study, formal sample size calculation is not required. We will therefore aim to recruit 40 patients (in keeping with recommendations^42^), 20 in each arm, with progression to a future RCT dependent on meeting set criteria relating to participant recruitment and retention rates as above. If the percentage of patients completing the study is 85%, 40 patients will give a 95% CI (70.2 to 94.3).

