### Statistical methods

The analysis of the primary outcome of the proportion of approached patients who complete the study successfully will include the proportion of eligible approached patients who consented, received the allocated intervention, completed both CPET tests and did not withdraw, with 95% CIs. As part of the intention-to-treat approach, those who have graft failure, die, or are lost to follow-up will be included in the analysis of the primary outcome as not completing the study successfully. The component proportions and the corresponding 95% CIs of the primary outcome will be presented as secondary outcomes.

The secondary feasibility outcomes of recruitment rate by trial site and the proportion of participants who were compliant with wearing wrist accelerometers, and their 95% CIs, will also be presented. Compliance to wearing the monitor will be assessed by measuring wear time. The days from providing consent to first CPET and the days from CPET to fistula disconnection will be summarised, and the median and IQR presented. Patient and healthcare professional perceived acceptability of the trial design and processes will be analysed using qualitative analysis.

Descriptive statistics of the secondary clinical outcomes will be presented for each arm separately, at baseline, the 6-month assessment, and the average change over time, with 95% CIs. Peak VO_2_ will also be presented by fistula site and according to prespecified flow rate categories. Very limited hypothesis testing will be conducted but mixed linear regression will be used to examine any difference in peak VO_2_ at 6 months between the two treatment arms, with adjustment for fistula site, flow rate, baseline peak VO_2_ and centre. Fistula-related symptoms will be assessed using the modified VASQoL questionnaire for all participants at enrolment and at 6 months for the standard care arm and compared where applicable. The proportion of participants who experienced at least one MACE by 6 months will be presented (alongside 95% CIs), and details of all reported MACEs listed. In addition, summaries of all secondary safety outcomes will be presented by arm.

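### The within-arm change summary planned for SF-36 perceived health change is a change of a change, and can be zero or negative when patients report improvement

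*Protocol article*

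**What the plan says.** Three places in the protocol article combine.

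- **Clinical outcome measures** names the additional SF-36 domains as "physical role limitation, emotional role limitation, energy/ fatigue, emotional well-being, social functioning, pain, general health, perceived health change". Perceived health change sits in this list with no separate handling.
- **Outcomes** defines the clinical outcomes as "clinical measures that will be measured at baseline and 6 months following intervention, and the differences in these values".
- **Statistical methods** says that the secondary clinical outcomes will be "presented for each arm separately, at baseline, the 6-month assessment, and the average change over time, with 95% CIs".

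The article does depart from this general rule elsewhere. MACE is reported as a proportion of participants by 6 months. The modified VASQoL is collected at 6 months only under standard care and is compared only where that is possible. Perceived health change gets no such departure.

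The only model named is a mixed linear regression for peak VO2; no test is named for any SF-36 domain. The article gives neither the recall period nor the scoring of the perceived health change item.

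**The concern.** For a state domain such as pain or social functioning, the 6-month value minus the baseline value measures what happened during follow-up. Perceived health change is a different kind of item: each answer is itself a statement about change. The baseline answer describes the time before enrolment, not health at enrolment. Subtracting it compares two rates of change, one ending at 6 months and one ending at baseline, and does not measure improvement since baseline.

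The per-arm table would then carry a mean and a 95% CI that a reader would naturally take as improvement or decline since baseline. The sign can mislead. Recipients may enter from 1 year after transplantation, so some may report a good recovery at baseline and little further change at 6 months. The table would show them as declining, although no decline was reported.

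**Working it through.** **The plan's own figures.** The article states no figure for this item. Its one statistical figure, the interval in Sample size for 85% completion among 40 patients, reproduces: the exact Clopper-Pearson interval for 34/40 is 70.2% to 94.3%. The present point does not depend on it.

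**Step 1: sign of the planned difference.** Let C0 and C6 be the ratings at baseline and 6 months on any ordered scale with a no-change value m. The planned quantity is D = C6 − C0. Improvement at 6 months means C6 > m, but the sign of D depends on C0, not on m. So D = 0 whenever the two answers are equal, and D < 0 whenever the second improvement is rated smaller than the first. This needs only the item's name and an ordered scale.

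**Step 2: illustration.** Assumption, not in the article: five levels scored 0, 25, 50, 75, 100, with 50 = no change.

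| Baseline | 6 months | Reported at 6 months | D |
|---|---|---|---|
| 50 | 75 | better | +25 |
| 75 | 75 | better | 0 |
| 100 | 75 | better | −25 |
| 75 | 50 | no change | −25 |
| 0 | 25 | worse | +25 |

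Of the 5 × 5 = 25 possible answer pairs, 5 × 2 = 10 report improvement at 6 months. D is positive in 7 of these, zero in 2 (75 to 75, 100 to 100) and negative in 1 (100 to 75). Of the 10 pairs reporting worse health at 6 months, 1 has a positive D (0 to 25). These are counts of possible pairs, not probabilities.

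**Step 3: what D estimates.** Treat a rating as the difference in health H over a look-back of R months. R is not stated; 6 to 12 is assumed. Then

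D = [H(6) − H(6−R)] − [H(0) − H(−R)] = [H(6) − H(0)] − [H(6−R) − H(−R)].

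The first bracket on the right is the true 6-month change, so D equals it only when H(6−R) = H(−R).

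- Steady gain of 5 points per 6 months: D = 5 − 5 = 0 for any R, against a true change of +5.
- Gain of 20 in months −12 to −6, flat to baseline, then +5: with R = 6, D = 5 − 0 = +5; with R = 12, D = 5 − 20 = −15. The true change is +5.
- H(−12) = H(−6) = 50, H(0) = 70, H(6) = 75, R = 12: D = 25 − 20 = +5, equal to the true change although health rose 20 points within the look-back.

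**Step 4: between arms.** Randomisation gives both arms the same expected C0. Hence E[D, ligation] − E[D, standard care] = E[C6, ligation] − E[C6, standard care]. The artefact cancels in expectation from a between-arm contrast and remains in each within-arm mean.

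**The case against.** The strongest reply is that the useful number is already planned. Statistical methods presents the 6-month value for each arm, so a reader can take the perceived-change result directly from it. That stands: the difference is one of three descriptive summaries, and it would be wrong to infer that it is the only figure reported.

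A second reply is that the general sentence is an umbrella that gives way item by item, as for MACE and VASQoL, and that tabulating one SF-36 item is detail for the analysis plan. The first half is correct: not every outcome is treated alike. But the article states a rule, departs from it where it does not fit, and leaves it in force here. That is a rule fixed badly, not a detail left out.

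Third, the recall period and scoring are not in the article, so every number in steps 2 and 3 is illustrative. That stands too. The sign problem in step 1 does not need them.

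Fourth, the 6-month rating is not a perfect measure either. With R = 12 it covers H(6) − H(−6), which includes six pre-trial months; under the steady-gain case it gives +10 against a true +5. This limits how the rating may be read, but the rating at least measures what its label says.

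A reader might go further and infer that the treatment comparison is biased, that the full-scale trial would be mis-sized, or that only patients stable throughout the look-back get a correct value. The documents and the algebra support none of these. Step 4 removes the first. Objectives says that recruitment and retention findings will inform design and powering, and nothing gives this item a role in choosing or sizing an outcome. The third fails because the condition is H(6−R) = H(−R), as the last example in step 3 shows.

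**Conclusion.** Wrong as written, and minor. Read as stated, the plan produces a per-arm change, with a 95% CI, for an item that already rates change. That summary does not measure improvement since baseline: it is zero for equal reported improvement at both visits and negative for a smaller one at 6 months. The conclusion rests on the item's name and on an ordered response scale; no particular recall period or scoring is needed.

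The reach is one summary of one additional descriptive domain in a 40-patient feasibility study. The primary outcome, progression criteria and sample size do not change.

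**What to change.** Add one sentence to Statistical methods that exempts perceived health change from the change-from-baseline summary. Report the 6-month rating by arm with its 95% CI as the perceived-change result, and show the baseline rating only as a description of the pre-trial course. The 6-month difference between arms may be added as a descriptive estimate, without a test. Keep change from baseline for the other SF-36 domains.

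No data, visits or patients are added. The small downside is that one domain is tabulated differently from the rest.

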#### Safety outcome measures

Surgical complications from fistula disconnection (number in each Clavien-Dindo classification^41^).Fistula-related complications in the standard care group.Transplant failure (return to permanent dialysis or retransplantation).Hospitalisation (number of hospitalisations and cumulative days in hospital).Patient death (all cause).

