### Progression to full-scale RCT

This feasibility study aims to test the processes of a proposed future multicentre RCT and therefore we will use a traffic-light approach to determine trial progression according to the following indices:

Patient participation:Green: > 40% of approached patients consent to trial participation.Amber: Between 30% and 40% of approached patients consent.Red: < 30% of patients consent.Adherence to randomisation and study completion:Green: > 85% of enrolled participants received the allocated intervention and completed both CPETs without withdrawing.Amber: Between 75% and 85% completion rate.Red: < 75% completion rate.

We anticipate that a green light for the above indices will realise patient recruitment and retention rates within a future full-scale RCT to enable scheduled completion. In response to an amber trigger, the Trial Management Group (TMG) will develop strategies that specifically respond to potential issues with patient participation that have been highlighted by the qualitative analysis. We would not proceed to a full-scale trial if a red signal is triggered.

During this feasibility study, we expect that, once open, each of the participating centres recruits a minimum of one patient per month and that fistula disconnection is performed within 62 days of CPET. If not met, the TMG will attempt to identify and address systematic problems that may hinder the main RCT.

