### Randomisation

Randomisation of consenting participants will be stratified according to fistula site (wrist or elbow) and fistula volume flow (low or high), as determined by a pre-randomisation Doppler ultrasound of the fistula, and allocated in a 1:1 ratio to the intervention (surgical disconnection of fistula) or to standard care (continued conservative management) using an interactive web response system provided by Sealed Envelope. Fistula flow rate will be measured during baseline assessment visits and categorised as either low flow (wrist AVF: ≤800 mL/min, elbow AVF: ≤1400 mL/min) or high flow (wrist AVF: >800 mL/min, elbow AVF: >1400 mL/min). The research team will confirm to the clinical and surgical teams which arm of the trial the participant has been randomised to, with the intervention being performed by a vascular access/transplant surgeon within 62 days of completion of baseline assessments. Given the surgical nature of the intervention, there will be no blinding in this trial with all participants, clinical and research team members aware of which trial arm is assigned at randomisation.

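### Fistula-related complications are counted only in the standard care group, so those in ligation-arm patients who still have a fistula enter no access-specific safety outcome

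*Protocol article*

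**What the plan says.** The protocol article, under Safety outcome measures, has five items. Two concern the access itself: "Surgical complications from fistula disconnection (number in each Clavien-Dindo classification)" and "Fistula-related complications in the standard care group". The first is tied to the operation and names no arm; the second is tied to an arm. The other three (transplant failure, hospitalisation and all-cause death) carry no arm restriction.

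The Outcomes section sets one window for all of them: "safety outcome measures occurring between study consent and the 6-month assessment visit". Statistical methods then states that "summaries of all secondary safety outcomes will be presented by arm".

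On timing, the Randomisation section has surgery done "within 62 days of completion of baseline assessments". The section on progression to the full trial treats this as an expectation that may be missed: "fistula disconnection is performed within 62 days of CPET. If not met, the TMG will attempt to identify and address systematic problems". Receipt of the allocated intervention is itself a feasibility outcome and forms part of the second traffic-light criterion, so the plan foresees that some patients may not receive it.

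**The concern.** The outcome is restricted by allocation, whereas the risk depends on whether the patient still has a fistula. A ligation-arm patient whose fistula clots, bleeds or becomes infected before surgery has had a fistula-related complication inside the safety window. It is not in the standard care group, and it did not arise from the disconnection operation, so neither access-specific item counts it. The same holds to 6 months for a ligation-arm patient who is never operated on.

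In the by-arm table, the ligation column for this item is empty by definition and not by observation. The summary then understates the access-related harm of the ligation strategy, part of which is the wait. The study is meant to mirror the full trial and test its processes. Fistula events during the wait are useful for that purpose, because they bear on how the wait is planned and may explain why an allocated operation did not take place. An arm-restricted definition could also be carried forward into the full trial.

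**Working it through.** The plan gives no figure for this item. Its one precision statement (85% of 40, with a 95% CI of 70.2 to 94.3) reproduces as an exact Clopper-Pearson interval for 34/40 (70.16% to 94.29%), but nothing here depends on it. The check has two parts.

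**1. Does any access-specific item count the event?** Take a ligation-arm patient with a fistula complication before surgery.
- Safety window: inside it, since the window opens at consent.
- Surgical complications item: not counted, since no operation has caused it.
- Fistula-related complications item: not counted, since the patient is not in the standard care group. That *group* means allocation is supported by the clinical outcomes list, where the 6-month fistula symptom questionnaire is limited to those randomised to standard care.
- Hospitalisation, transplant failure, death: counted if the event leads to one of these, but not labelled as fistula-related.

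**2. How much time with a fistula is left out?**

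Inputs from the article: 20 patients per arm; wait up to 62 days from baseline; follow-up 6 months, about 182.6 days. The Abstract places the second exercise test 6 months after the first, while the Outcomes section speaks of 6 months following intervention, so both readings are shown.
- Six months from baseline: 62 / 182.6 = 34%.
- Six months from surgery: 62 / (62 + 182.6) = 62 / 244.6 = 25%.

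Patient-days in the ligation arm, with the window running from baseline (total 20 × 182.6 = 3652):

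| Scenario | Days with a fistula | Share of arm's time |
|---|---|---|
| All operated on at day 31 (assumed) | 20 × 31 = 620 | 17% |
| All operated on at day 62 | 20 × 62 = 1240 | 34% |
| 3 of 20 never operated on (assumed), others at day 31 | 17 × 31 + 3 × 182.6 = 1075 | 29% |
| 3 of 20 never operated on (assumed), others at day 62 | 17 × 62 + 3 × 182.6 = 1602 | 44% |

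Time from consent to baseline assessments is also inside the safety window and would add to every row.

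Expected uncounted events = 20 × (62 / 182.6) × rate per 6 months. The documents give no rate, so a range is assumed:
- 5%: 20 × 0.34 × 0.05 = 0.34
- 10%: 20 × 0.34 × 0.10 = 0.68
- 20%: 20 × 0.34 × 0.20 = 1.36

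At a 31-day wait these halve (0.34 at the 10% rate). A patient who is never operated on contributes 0.10 events at the 10% rate (0.05 to 0.20 over the range).

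**The case against.** The strongest reply is that this is a descriptive feasibility study of 40 patients in which each strategy's characteristic harm is reported: surgery for one arm, a retained fistula for the other. The label says openly that the item concerns standard care, so nobody is told that the ligation arm had zero events. No between-arm safety test is planned; the one named model is for peak VO2. The expected number of missed events is around one or fewer over most of the assumed range, and the upper figure needs every patient to wait the full 62 days. All of this is fair as to size. It does not remove the gap, because the plan also commits to presenting every safety outcome by arm over a window that includes the wait.

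Several stronger readings are tempting, and the article does not support them.
- *The plan breaks its own intention-to-treat rule for safety.* The article uses that term only for how graft failure, death and loss to follow-up count in the primary outcome. For safety it promises only a summary by arm.
- *The whole safety picture counts different harms in each arm.* Three of the five outcomes apply to both arms. Surgical complications are not restricted by arm either, so a clinically indicated disconnection in a control patient already fits that item.
- *The events are lost.* An event causing admission or death is still counted there. Non-receipt of surgery and days from CPET to disconnection are also recorded, so an event that delays or prevents surgery leaves a trace. What falls outside the listed outcomes is the labelled count and any milder event. Whether general adverse event recording would catch those is a matter for the full protocol, which is not shown.

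**Conclusion.** The point holds as a defect in one outcome definition. The restriction is written into the outcome, so it is not a detail that the article left to a fuller document. Followed as written, it omits ligation-arm fistula events from both access-specific counts, and the error can run in one direction only: it understates access-related harm in the ligation arm.

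The size is modest. For patients operated on by day 62, the uncovered time is up to about 34% of a 6-month window from baseline, or 25% if the 6 months run from surgery. It is longer once the time before baseline, late surgery or non-receipt is added. If all 20 patients wait 62 days, this is about 0.3-1.4 events at an assumed 5-20% per 6 months; both the rate and the uniform full wait are assumptions. That some patients may never be operated on is inferred from the feasibility outcomes and progression thresholds. No non-receipt rate is given, and the 85% threshold also covers CPET completion and withdrawal.

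A reader might infer that the trial's main conclusions are at risk. They are not: the primary outcome, the progression criteria and the single planned test do not use this item. It is still worth correcting, because the change is cheap and the definition may pass to the full trial.

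**What to change.** Reword the item to: *Fistula-related complications in all participants, from consent to the 6-month assessment*. Report it by allocated arm and split it into events before and after any disconnection. Starting at consent keeps the item in step with the other safety outcomes; starting at randomisation would give this one item a different window and drop events between consent and randomisation.

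The surgical complications item needs no change, since its wording already covers a disconnection in either arm.

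The cost is one line of outcome wording and slightly more event recording in the ligation arm. Visits, procedures, sample size and clinical management stay as they are.
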